### Consent

Patients with the capacity to give consent will be approached directly. If the patient is unable to write (eg, dominant hand weakness, dyspraxia and ataxia), witnessed verbal consent (or a mark made by the participant with intent to sign) may be recorded on the consent form. If a participant lacks the mental capacity to provide consent due to decreased consciousness or aphasia, the investigator or nominee will approach the patient’s relative (or other personal legal representative such as partner or close friend) to seek consent (figure 1). If this is not possible, then an independent medical practitioner not associated with the trial will be approached for proxy consent.^23^ Full informed consent is later sought from the recruited participant within 72 hours if mental capacity is regained (figure 1).

**Figure 1 F1:**
[figure not shown]
Flowchart for the process of consent.

It will be explained to the patient or their legal representative that enrolment into the trial is entirely voluntary and they can withdraw at any time without giving a reason.

### Randomisation

All participants eligible for inclusion and for whom consent will be obtained will be randomised in real time over a secure internet site with minimisation on prognostic factors including age, time since stroke onset, limited GCS and visual estimate of maximum haematoma diameter.

In the event that the trial website cannot be accessed or server failure occurs, investigators will follow the working practice document for disaster recovery, which will allow the participant to be randomised following a standard operating procedure.

The unpredictable allocation sequence will be generated and programmed into the computerised randomisation system. The research team at each site will conduct the randomisation via secure log-ins to the web-based system. Randomisation using a minimisation algorithm (age<70 years or older, time to randomisation<24 hours, limited GCS score 2–6, ICH diameter 4 cm or greater) and release of allocation only after enrolment, consent and baseline data collection will ensure allocation concealment.

This trial will compare two doses of mannitol versus standard care including monitoring of participants before, during and after treatment, collection of key clinical assessments and presence or absence of adverse effects. It is not feasible for participants and researchers/investigators to be blinded due to the open-label design. Clinical staff preparing and administering mannitol will also not be blinded to treatment allocation. However, follow-up assessments and adjudication of brain imaging will be conducted centrally by assessors blinded to randomisation and treatment allocation.

As this is an unblinded trial, code-breaking will not be required. If a contra-indication to mannitol develops after randomisation (eg, anuria or severe congestive cardiac failure), the trial treatment should be stopped. In order to minimise bias that could be introduced through knowledge of which treatment the participant has received, unblinded staff will be kept to a minimum and will be asked not to reveal treatment allocation to anyone.

### Intervention

Participants will be enrolled equally into one of three groups (figure 2) as soon as possible after randomisation:

Arm 1: 1 g/kg 10% single-dose mannitol infusion at 10 mL/min, in addition to standard care.Arm 2: 1 g/kg 10% mannitol at 10 mL/min followed by a second dose 1 g/kg repeated at 24 hours, if the serum osmolality is <320 mOsm/kg and sodium<160 mmol/L after the first dose, in addition to standard care.Arm 3: standard care alone.

**Figure 2 F2:**
[figure not shown]
Trial flowchart. ICH, intracerebral haemorrhage; IV, intravenous; GCS, Glasgow Coma Scale; NIHSS, National Institutes of Health Stroke Score; TICS-M, Telephone Interview of Cognitive Status; NG, nasogastric; e-GFR, estimated Glomerular Filtration Rate; UTI, Urinary Tract Infection; EQ-5D, European Quality of Life 5 Dimensions score; EQ-VAS, EuroQoL Visual Analogue Scale.

### Assessments

Participants will be assessed clinically at baseline (demographics, medical history, investigations, diagnosis of ICH) in line with local clinical practice and preinfusion (day 1) and end of treatment (day 1–2) for Arms 1 and 2. All participants will be assessed again on day 5 (±2), hospital discharge and on day 180 to gather information on interventions, adverse events, discharge data and discharge destination. Data collection forms can be found in online (https://stroke.nottingham.ac.uk/mace-ich/docs/).

All participants will have brain imaging (CT head) as part of routine care before enrolment. A second research CT head will be performed at day 5 (±2) after intervention to measure haemorrhage volume and oedema volume. The methods of scan analysis are detailed in the online supplemental document.

#### Blood tests

All participants will have blood tests taken as part of routine clinical care at the time of presentation whether or not they go on to participate in the trial. Blood samples will be labelled and analysed locally at each hospital site in accordance with local practice. Each participant in Arms 1 and 2 will have one blood test for urea and electrolytes (U&Es) and serum osmolality after the infusion, and the results will be made available to the treating clinical team. Participants in Arm 2 will have a further blood test after the second infusion (figure 2).

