**Methods:**

The mannitol for cerebral oedema after acute intracerebral haemorrhage trial (MACE-ICH) aims to include 45 ICH participants from 10 UK sites with estimated largest diameter of haematoma volume >2 cm, presenting within 72 hours of onset with, or at risk of, cerebral oedema (limited Glasgow Coma Scale (GCS)<9, including motor and visual components only, and National Institutes of Health Stroke Scale>8) with or without mass effect. Participants will be randomised (1:1:1) to 1 g/kg 10% single-dose intravenous mannitol, 1 g/kg 10% mannitol followed by a second dose at 24 hours, or standard care alone. Outcome assessors will be masked to treatment allocation. Feasibility outcomes include proportion of patients approached being randomised, participants receiving allocated treatment, recruitment rate, treatment adherence and follow-up. Secondary outcomes include serum electrolytes and osmolality at days 1–2; change in ICH and oedema volume at day 5; number of participants who developed urinary tract infection, GCS and National Institutes of Health Stroke Scale at day 5±2; length of hospital stay, discharge destination and death up to day 28; death and death or dependency by day 180 and disability (Barthel Index), quality of life (EuroQol, 5-D) and cognition (telephone mini-mental state examination) at day 180.

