### Outcomes

The primary outcome is based on feasibility: number of patients screened, rate of eligible patients randomised and reasons for non-randomisation, participants who received allocated treatment and adherence to intervention, proportion of participants followed up to day 180 and reasons for loss to follow-up, proportion of randomised participants with full outcome data and reasons for non-availability.

The following measures are expected to be secondary outcomes in a definitive trial and will be collected:

Day 1–2: U&Es; eGFR; serum osmolality to correlate response to mannitol.Day 5±2: neurological deterioration (increase in NIHSS>3); GCS; NIHSS; death; urinary tract infection; sepsis.Radiological: follow-up CT after treatment (day 5±2) for comparison with pre-enrolment imaging to assess changes in oedema volume, haematoma size/volume, maximum diameter, midline shift and hydrocephalus.Day 28: mortality; urinary tract infection; septicaemia.Day 180 (blinded central follow-up via telephone/postal interview): death or dependency (mRS) disability (Barthel Index); mood (Zung depression scale); cognition (Telephone Interview of Cognitive Status); quality of life (EuroQol 5-D); length of stay; discharge destination. The long-term outcomes post-COVID-19 and ICH are not yet fully defined and may include additional yet undefined neurological complications. These will also be collected.Number of patients transferred to the high dependency unit.Number of patients intubated and ventilated.Number of patients who underwent neurosurgical intervention.Recurrent stroke (ischaemic or haemorrhagic).

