### Adverse events

All adverse events on days 0–1 (including during infusion, Arms 1 and 2 only) and for 24 hours post-treatment will be collected. All adverse events will be assessed for seriousness, expectedness and causality by adjudicators masked to treatment allocation. Serious adverse events (SAEs) will be categorised in accordance with the medical dictionary for regulatory authorities. All SAEs will be collected until day 28, and fatal SAEs and safety outcome events (thrombophlebitis, hyper/hyponatraemia, pulmonary oedema, hypotension, renal impairment) will be collected until day 180.

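### Post-randomisation electrolytes and osmolality are scheduled once in Arm 1, up to twice in Arm 2 and not in Arm 3, so the day 1–2 outcome has no scheduled standard-care comparator and laboratory-defined harms are detected unequally

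*Protocol article*

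**What the plan says.** The Blood tests section of the protocol article treats the arms differently. For everyone it mentions one set of bloods: "All participants will have blood tests taken as part of routine clinical care at the time of presentation". After that, "Each participant in Arms 1 and 2 will have one blood test for urea and electrolytes (U&Es) and serum osmolality after the infusion", and "Participants in Arm 2 will have a further blood test after the second infusion". The Intervention section makes the second infusion depend on osmolality and sodium after the first, so two tests in Arm 2 is a maximum. No post-randomisation test is scheduled for Arm 3.

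The Assessments section agrees. After baseline it lists "preinfusion (day 1) and end of treatment (day 1–2) for Arms 1 and 2"; the next visit for all participants is day 5 (±2), and no bloods are mentioned there.

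The outcome lists carry no such restriction:

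- Abstract, Methods: "Secondary outcomes include serum electrolytes and osmolality at days 1–2".
- Outcomes: "Day 1–2: U&Es; eGFR; serum osmolality to correlate response to mannitol", placed among measures foreseen as secondary outcomes of the definitive trial.
- Adverse events: "safety outcome events (thrombophlebitis, hyper/hyponatraemia, pulmonary oedema, hypotension, renal impairment) will be collected until day 180".

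The Statistical analysis section says that the analysis is descriptive and that anything done by treatment group is exploratory.

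**The concern.** Abnormal sodium and impaired renal function are found mainly by taking blood. If the trial takes blood more often in one arm than in another, that arm will tend to record more such events even when the treatment does nothing. Here the scheduled intensity runs 0, 1, up to 2 from standard care to two doses, which is the order in which a true dose effect would appear.

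Two things are at stake. First, a day 1–2 change in sodium, osmolality or eGFR after mannitol cannot be set against the natural course of severe intracerebral haemorrhage, because no matching standard-care value is scheduled. Second, counts of laboratory-defined harms by arm are not comparable. Masked adjudication, described under Adverse events, does not repair this, since adjudicators see only the events that were detected. The Data Monitoring Committee reviews unblinded safety data every 6 months (Trial management), so the imbalance could affect ongoing oversight as well as the final tables.

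**Working it through.** The article gives no figure on this point and states that no formal sample size calculation was done, so there is nothing to reproduce. The check counts scheduled tests and then illustrates what they would find if mannitol had no effect.

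**Inputs**

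- 45 participants randomised 1:1:1 (Abstract, Methods): 45/3 = 15 per arm.
- Trial-ordered post-randomisation tests per participant, k: 1 in Arm 1, at most 2 in Arm 2, 0 in Arm 3 (Blood tests, Intervention).
- Chance p that one test is abnormal, the same in every arm: not in the document; assumed to be 5%, 10% or 20%.

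**Step 1: number of scheduled tests.** Arm 1: 15 × 1 = 15. Arm 2: 15 × 2 = 30 if everyone has the second infusion; 15 + 15 × 0.8 = 27 or 15 + 15 × 0.5 = 22.5 if 80% or 50% do (assumed). Arm 3: 0.

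**Step 2: expected participants with at least one abnormal result, no drug effect.** With independent tests this is 15 × [1 − (1 − p)^k]. With perfectly correlated tests a second sample adds nothing, so Arm 2 gives 15 × p. Two samples from one person about a day apart should lie between these limits. The Arm 2 column assumes that all have both tests.

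| Assumed p | Arm 1 | Arm 2 (perfectly correlated to independent) | Arm 3 |
|---|---|---|---|
| 5% | 0.75 | 0.75 to 1.46 | 0 |
| 10% | 1.50 | 1.50 to 2.85 | 0 |
| 20% | 3.00 | 3.00 to 5.40 | 0 |

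For example, at 10% with independent tests, Arm 2 is 15 × (1 − 0.9²) = 15 × 0.19 = 2.85.

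**Step 3: chance that an arm records at least one case, p = 10%.** Arm 1: 1 − 0.9^15 = 0.794. Arm 2: 0.794 (perfectly correlated) to 1 − 0.9^30 = 0.958 (independent). Arm 3: 0 from trial-ordered tests.

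**Step 4: allowance for ward bloods in Arm 3.** If a share r of Arm 3 has one routine test whose result reaches the trial, the expected count is 15 × p × r. At p = 10% this is 0.75 for r = 0.5 and 1.5 for r = 1. The latter equals the Arm 1 figure and the lower limit for Arm 2. Ward bloods taken in the mannitol arms would add to their counts too.

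**Step 5: equal testing.** With two common time points in every arm the counts become 30, 30 and 30. The expected number is then the same in each arm: at 10%, 2.85 under independence (1.46 at 5%, 5.40 at 20%).

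The gap between mannitol and standard care in trial-ordered tests is present whatever the correlation. The gradient from Arm 1 to Arm 2 depends on it and vanishes at the lower limit.

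**The case against.** The strongest reply is that the day 1–2 bloods were never meant for comparison with standard care. The Outcomes section ties them to response to mannitol, and the first post-dose result also decides whether the second infusion is given. That reading is plausible and may explain the day 1–2 outcome. It does not explain the safety outcomes, which are listed for the whole trial and depend on the same tests.

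Four stronger readings may tempt a reader, and the article does not support them:

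- *There is no comparator at all.* Arm 1 can be compared with Arm 2 after the first dose, and change from presentation values is possible, although the article does not say that osmolality is measured at presentation in everyone. Only a scheduled standard-care comparator is absent.
- *Arm 3 has no bloods after presentation.* The article does not say so. Later ward bloods are not excluded, and an abnormality found on them could be reported as a safety event up to day 180. What is absent is a scheduled, time-matched value. The trial flowchart, the data collection forms and the full protocol are not shown and might add something, though the visible text is consistent.
- *Testing frequency alone must produce a dose-response.* That requires imperfect correlation between the two Arm 2 tests and little Arm 3 detection. Neither is known.
- *The safety tables will decide whether one or two doses go forward.* No section says this. The Discussion already foresees a definitive trial comparing both regimens with standard care.

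The descriptive, exploratory status of the analysis also counts against a severe rating: no primary outcome comparison or error rate depends on these results. A descriptive count by arm still misleads if detection differs by arm.

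**Conclusion.** The concern holds at moderate severity. The schedule and the outcome lists do not match: laboratory outcomes and laboratory-defined harms are stated for the trial as a whole, while the trial-ordered tests behind them number one in Arm 1, up to two in Arm 2 and none in Arm 3. Detection therefore favours finding harm in the mannitol arms regardless of any drug effect.

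At an assumed 10% per test, the expected counts are 1.5, 1.5 to 2.85, and 0 of 15 in Arms 1, 2 and 3. These figures rest on the assumed p, on full receipt of the second infusion in Arm 2 and on no Arm 3 result reaching the trial. They show the direction and possible scale and do not predict what will be seen. The absence of a scheduled Arm 3 test rests on the text alone.

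**What to change.** 1. In all three arms, record U&E and eGFR results, and osmolality where measured, from the routine inpatient bloods nearest common times after randomisation (about 24 h and about 48 h), alongside the trial samples.
2. Limit between-arm comparison of hyper/hyponatraemia and renal impairment to those common times.
3. Report the number of tests, and of participants with a result, by arm.
4. List separately any abnormality found only on the extra mannitol-arm samples.

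If Arm 3 values cannot be obtained, state that the day 1–2 laboratory outcome applies to the mannitol arms only, and make no comparison of laboratory-defined harms with standard care.

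The cost is data entry for all arms, including a second time point in Arm 1, at most 45 × 2 = 90 sets of results. No new procedure is needed. Because the remedy uses results already in hospital records, it remains possible late in a recruitment period that the Trial design section runs from February 2024 to November 2025. Two drawbacks remain: osmolality will be incomplete in Arm 3, and clinician-ordered bloods may come from selected participants, which is why the numbers tested must be shown.

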### Outcomes

The primary outcome is based on feasibility: number of patients screened, rate of eligible patients randomised and reasons for non-randomisation, participants who received allocated treatment and adherence to intervention, proportion of participants followed up to day 180 and reasons for loss to follow-up, proportion of randomised participants with full outcome data and reasons for non-availability.

The following measures are expected to be secondary outcomes in a definitive trial and will be collected:

Day 1–2: U&Es; eGFR; serum osmolality to correlate response to mannitol.Day 5±2: neurological deterioration (increase in NIHSS>3); GCS; NIHSS; death; urinary tract infection; sepsis.Radiological: follow-up CT after treatment (day 5±2) for comparison with pre-enrolment imaging to assess changes in oedema volume, haematoma size/volume, maximum diameter, midline shift and hydrocephalus.Day 28: mortality; urinary tract infection; septicaemia.Day 180 (blinded central follow-up via telephone/postal interview): death or dependency (mRS) disability (Barthel Index); mood (Zung depression scale); cognition (Telephone Interview of Cognitive Status); quality of life (EuroQol 5-D); length of stay; discharge destination. The long-term outcomes post-COVID-19 and ICH are not yet fully defined and may include additional yet undefined neurological complications. These will also be collected.Number of patients transferred to the high dependency unit.Number of patients intubated and ventilated.Number of patients who underwent neurosurgical intervention.Recurrent stroke (ischaemic or haemorrhagic).

### Adverse events

All adverse events on days 0–1 (including during infusion, Arms 1 and 2 only) and for 24 hours post-treatment will be collected. All adverse events will be assessed for seriousness, expectedness and causality by adjudicators masked to treatment allocation. Serious adverse events (SAEs) will be categorised in accordance with the medical dictionary for regulatory authorities. All SAEs will be collected until day 28, and fatal SAEs and safety outcome events (thrombophlebitis, hyper/hyponatraemia, pulmonary oedema, hypotension, renal impairment) will be collected until day 180.

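### Part of the adverse-event collection window is timed from the end of treatment, so counts of non-serious events are not like for like across the three arms

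*Protocol article*

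**What the plan says.** The Adverse events section sets three windows.

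- All adverse events, including non-serious ones: "All adverse events on days 0–1 (including during infusion, Arms 1 and 2 only) and for 24 hours post-treatment will be collected".
- Serious adverse events (SAEs): "All SAEs will be collected until day 28, and fatal SAEs and safety outcome events" is the start of a sentence that makes no distinction between arms.
- Fatal SAEs and named safety outcomes: the same sentence ends "hyper/hyponatraemia, pulmonary oedema, hypotension, renal impairment) will be collected until day 180", again for all arms alike.

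The Intervention section gives Arm 1 "1 g/kg 10% single-dose mannitol infusion at 10 mL/min, in addition to standard care". Arm 2 receives the same infusion, "followed by a second dose 1 g/kg repeated at 24 hours, if the serum osmolality is <320 mOsm/kg" and sodium is also below its limit. Arm 3 has standard care alone.

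The Assessments section lists early clinical assessments "preinfusion (day 1) and end of treatment (day 1–2) for Arms 1 and 2". All participants are then seen at day 5 (±2). For imaging it says: "A second research CT head will be performed at day 5 (±2) after intervention". The Outcomes section also describes this scan as following treatment.

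**The concern.** A window that closes 24 h after treatment closes at different times when treatment itself lasts different times. Arm 2 has its second dose a day after the first, so its window runs about a day longer than Arm 1's. In Arm 3 there is no treatment end to count from.

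If the first days after a severe haemorrhage bring frequent background events, the arm watched longest will show the most, even if mannitol does nothing. A table of non-serious events by arm could then show an excess in the two-dose arm that is only observation time. The Data Monitoring Committee reviews unblinded safety data, and the results are meant to inform a definitive trial, so such a table would have readers.

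The window in Arm 2 also depends on a laboratory result after randomisation. A participant whose second dose is withheld has, on the literal wording, the shorter Arm 1 window.

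**Working it through.** The article gives no window length or event count to reproduce, so the check builds the windows from the stated rules.

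**Inputs.** Dose 1 g/kg of a 10% solution at 10 mL/min, and second dose at 24 h (Intervention). Weight 70 kg, the average patient used in the Discussion; 50 and 100 kg are assumed as a range. 45 participants allocated 1:1:1 (Abstract), so 45 / 3 = 15 per arm. Assumptions: the 24 h to the second dose runs from the start of the first infusion, the second dose is given, and days 0–1 starts at the first infusion (in Arm 3, at the equivalent moment).

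**Step 1, infusion time.** 1 g/kg ÷ 0.1 g/mL = 10 mL/kg. At 70 kg that is 700 mL, and 700 / 10 = 70 min = 1.17 h.

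**Step 2, the part tied to treatment**, from the start of the first infusion:

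- Arm 1: 1.17 + 24 = 25.17 h
- Arm 2: 24 + 1.17 + 24 = 49.17 h
- Arm 3: undefined

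The ratio of Arm 2 to Arm 1 is 49.17 / 25.17 = 1.95. It is 1.97 at 50 kg (48.83 / 24.83) and 1.94 at 100 kg (49.67 / 25.67).

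**Step 3, total observation.** Each arm is observed until the later of the end of days 0–1 and the end of the part tied to treatment.

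| Days 0–1 read as | Arm 1 | Arm 2 | Arm 3 | Arm 2 / Arm 1 | Arm 2 / Arm 3 |
|---|---|---|---|---|---|
| 24 h | 25.17 h | 49.17 h | 24 h | 1.95 | 2.05 |
| 48 h | 48 h | 49.17 h | 48 h | 1.02 | 1.02 |

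The numbering in Assessments does not choose between the rows. It puts the pre-infusion assessment on day 1 and the end of treatment on day 1–2, whereas Adverse events speaks of days 0–1. If the first infusion falls on day 1, Arm 2's second dose falls on day 2, after days 0–1 have closed, and the Arm 1 and Arm 2 figures of the first row apply. If the clock starts at the first infusion and covers two full days, the second row applies.

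**Step 4, effect on counts with no drug effect.** With the same constant risk p per 24 h in every arm, the expected number of participants with an event over t hours is 15 × [1 − (1 − p)^(t/24)]. The article gives no value for p, so these are assumed.

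| Assumed 24-h risk | Arms 1 / 2 / 3, 24-h reading | Arms 1 / 2 / 3, 48-h reading |
|---|---|---|
| 10% | 1.6 / 2.9 / 1.5 | 2.8 / 2.9 / 2.8 |
| 20% | 3.1 / 5.5 / 3.0 | 5.4 / 5.5 / 5.4 |
| 40% | 6.2 / 9.7 / 6.0 | 9.6 / 9.7 / 9.6 |

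At 20%, for instance, Arm 2 on the 24-h reading is 15 × [1 − 0.8^(49.17/24)] = 15 × 0.367 = 5.5.

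**Step 5, CT.** Time zero for the follow-up scan is undefined in Arm 3 and ambiguous in Arm 2. Counting from the last dose would move Arm 2 by about 1 day relative to Arm 1, within an allowed range of days 3 to 7.

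**The case against.** The case on the other side is substantial, and much of it stands as a limit on the point.

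- **Twice the observation is not established.** A reader might infer that Arm 2 is simply watched about twice as long. That is true of the part tied to treatment, but true of total observation only if days 0–1 means about 24 h. On the 48-h reading the excess is about 2%.
- **Arm 3 is not left unobserved.** The restriction to Arms 1 and 2 most naturally qualifies the words on infusion, so Arm 3 keeps days 0–1. Arms 1 and 3 then differ little (25.17 against 24 h), and a graded excess across all three arms does not follow from window length.
- **The day-5 visit is not tied to treatment.** It applies to all participants. Only the CT wording refers to the intervention, and a scan is a single time point, so the issue there is time zero and not length of observation.
- **The safety comparison as a whole is not compromised.** SAEs, fatal SAEs and the named safety outcomes have common calendar windows.
- **Dose choice is not at stake on the text.** The Discussion carries both regimens and standard care into the definitive trial. Nothing says that a regimen will be chosen on these counts.
- **The analysis is descriptive and exploratory**, and the article condenses a fuller protocol that may define time zero.

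The last objection does not dispose of the point. The rule for all adverse events is stated, not omitted, and followed as written it gives unequal windows. Calling a table exploratory does not make crude counts from unequal windows comparable.

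**Conclusion.** The point holds for adverse events collected only under the short window, in practice non-serious events outside the named safety outcomes. Part of that window is timed from the end of treatment: it closes at about 25 h in Arm 1 and 49 h in Arm 2, and has no meaning in Arm 3. Total observation in Arm 2 is 1.02 to 1.95 times that in Arm 1, and the article does not say where in that range the trial lies. At the upper end, and with an assumed 20% risk per 24 h, the artefact is about 2.4 extra participants with an event out of 15 in Arm 2 relative to Arm 1 (5.5 − 3.1). At the lower end it is about 0.1 (5.5 − 5.4).

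These figures rest on a 70 kg participant, a second dose that is given, a constant risk and no drug effect. The two day numberings need reconciling because they leave the range open, but they can be read together and are not a flat contradiction. No feasibility outcome or sample-size statement is affected.

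**What to change.** - Collect and tabulate all adverse events over one fixed window from randomisation, identical in the three arms and long enough to contain 24 h after Arm 2's second dose. With 72 h there is room for a delay of up to 72 − 49.17 = 22.8 h between randomisation and the first infusion at 70 kg.
- List infusion reactions separately, without comparison between arms.
- For participants already enrolled (recruitment began in February 2024), restrict between-arm tables to the window common to all arms. This needs recorded onset times.
- Time the day-5 (±2) CT from randomisation in all arms.
- Use one day-numbering convention in Assessments and Adverse events, and state what day 0 is.

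The cost is a change of wording, forms and table definitions, with a few more non-serious events to record in Arms 1 and 3. With a common window the ratios in the working become 1.00 by construction. The sample size does not change.
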